### Participants Support and Monitoring

To promote adherence to the REHEAT intervention and ensure accurate data collection, a combination of participant support and monitoring strategies is implemented throughout the study.

A dedicated “Help” section is included in the REHEAT app, allowing users to access online guides and directly contact the research team via email to receive support throughout the study.

A standardized 3-level notification system is also implemented to keep in touch with and better assist users in completing their tasks. First, participants receive real-time notifications on their smartphones whenever new data collection tasks become available or when scheduled diaries or tests are overdue. Push notifications also alert participants if Garmin data cannot be retrieved, indicating potential issues with device use or synchronization with the Garmin Connect application. Second, participants receive automated weekly reports every Monday morning, providing individualized feedback on their task completion, including weekly response rates for diaries and the overall percentage of Garmin device wear, while also highlighting expected targets to motivate continued engagement. Third, an automated daily report is generated for the research team, providing summary information on participants who are experiencing delays with specific tasks. This enables the team to identify and contact these participants, understand the reasons for non-response, and provide the necessary support.

### Outcomes

The REHEAT app integrates a comprehensive data collection system to evaluate both the implementation and the impact of a heatwave adaptation strategy in the experimental groups. Data are collected through digital wearable devices with physiological sensors, app usage logs, online surveys and cognitive tests, and environmental monitoring (Figure 3). Smartphones and smartwatches enable the passive collection of behavioral and physiological data, which are combined with self-reported information to capture a rich, multidimensional picture of participants’ experiences.

**Figure 3. fig3-00469580251405766:**
[figure not shown]
REHEAT data collection System and metrics.

A growing body of research highlights the advantages of integrating traditional survey methods with mobile and wearable technologies to gain more nuanced insights into individuals’ daily experiences and behaviors.^
45
^ These technologies support the continuous collection of high-resolution physiological and contextual data while minimizing the user burden, thus reducing recall bias and social desirability effects commonly associated with self-reports.^
46
^ The combination of “passive” sensing and traditional surveys allows for the joint analysis of objective indicators and subjective perceptions, including emotional states, routines, and situational appraisals.

The overall impact of the REHEAT strategy and the heterogeneity of its effects between groups is assessed through key primary outcomes, including strain accumulation, cognitive performance, emotional distress, sleep and night recovery, and mental and physical health. Secondary outcomes include objective and self-reported measures of intervention compliance, manipulation checks, and user experience and satisfaction. The complete list of study outcomes, along with detailed descriptions of their sources, data collection methods, and characteristics, is provided in Table 1.

**Table 1. table1-00469580251405766:** Summary of REHEAT Primary and Secondary Outcomes.

Outcome	Domain	Source	Time frame	Measurement description
*Primary outcomes*				
Strain accumulation	Physiological & psychological load	Garmin smartwatch; app-based questionnaires	Daily, with a focus on baseline vs heatwaves occurrence	Objective physiological heart rate metrics (HRV); self-reported stress (VAS)^ 47 ^ and daily activities
Cognitive performance	Cognitive function	App-based cognitive tests	Daily, with a focus on baseline vs heatwaves occurrence	Task-based cognitive performance via the short tests serial-seven^ 48 ^ and delayed recall^ 49 ^
Emotional distress	Psychological well-being	App-based questionnaires	Daily, with a focus on baseline vs heatwaves occurrence	Positive and Negative Affect (I-PANAS-SF)^ 50 ^
Sleep quality & quantity	Sleep and recovery	Garmin smartwatch; app-based questionnaires; pre- and post-intervention questionnaires	Daily, with a focus on baseline vs heatwaves occurrence; Middle term, pre- and post-intervention	Objective sleep duration and circadian rhythm; self-reported sleep quality and duration (B-PSQI, Karolinska sleep diary)^51,52^
Nighttime recovery	Physiological recovery	Garmin smartwatch; app-based questionnaires	Daily, with a focus on baseline vs heatwaves occurrence	Objective physiological heart rate metrics; self-reported recovery (Karolinska sleep diary)^ 51 ^
Mental & Physical Health	General health	App-based questionnaires; pre- and post intervention questionnaires	Daily, with a focus on baseline vs heatwaves occurrence; middle term, pre- and post-intervention	Self-reported injuries, general health, mental health (MHI-5),^53,54^ burnout (SMBM)^ 55 ^
*Secondary outcomes*				
Intervention Compliance	Engagement	App usage logs	Continuously during intervention	App interaction frequency and feature use tracked via in-app activity logs
Manipulation check	Health behavior	Garmin smartwatch; app-based questionnaires	Daily, with a focus on baseline vs heatwaves occurrence	Self-reported and objective indicators of coping behaviors for hydration, nutrition, peak-hour strenuous activity, etc.
User satisfaction & experience	User Experience	post-intervention questionnaire; interviews with subsample	Post-intervention	user experience questionnaire and qualitative interviews

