### Sample Size Calculation

We estimate the minimum sample size for a 2-arm, parallel-group superiority RCT with a continuous outcome and 1:1 allocation using the standard formula:

$$n=\frac{2\sigma^{2}{\left(Z_{\alpha /2}+Z_{\beta }\right)}^{2}}{\Delta^{2}}$$

where *n* is the required sample size per group, *σ* is the standard deviation of the outcome, ∆ is the expected difference (minimum clinically important difference) between groups, *Z_α/_*_2_ is the critical value for a 2-sided significance level (*α* = .05), and *Z_
_β_
_* is the critical value corresponding to 80% power.

To inform the parameters *σ* and ∆, we use empirical data from a previous observational study conducted by the REHEAT research team on a sample of 294 office workers in Canton Ticino (Southern Switzerland), monitored for 30 working days between February and April 2024.^
45
^ In that study, daily recovery was defined as the normalized difference between so-called “body battery levels” (a measure assessed by means of smartwatches) in the evening and at wake-up. A fixed-effects panel regression model is estimated, with recovery in body battery levels as the dependent variable and average daily temperature (from the Lugano MeteoSwiss station) as the main predictor, controlling for perceived health, weekday, and week number.

Due to the absence of days with average temperatures above 18^◦^C in that dataset, we extrapolate the expected effect of hot days by assuming a linear relationship between temperature and recovery. We use predicted average recovery values for moderate days (14°C-18°C, typical of June in Canton Ticino) as the baseline and compare them to predicted values at 25°C—the MeteoSwiss threshold for heat episodes.^
56
^ The resulting difference in recovery is used as the expected intervention effect (∆), under the assumption that the REHEAT strategy could fully mitigate the adverse impact of heat.

Although optimistic, this assumption is conservative in terms of sample size estimation: the effect size is derived from a lower-risk population (office workers) and under the assumption of linearity, whereas prior literature suggests that the impact of heat on health is often nonlinear and intensifies at higher temperatures.

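### The trial is sized for one endpoint at an undivided 5%, but six unordered primary domains are declared and the powered endpoint is not linked to any of them

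*Protocol article*

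**What the plan says.** **Primary outcomes.** The Outcomes section says the overall impact of the strategy "is assessed through key primary outcomes, including strain accumulation, cognitive performance, emotional distress, sleep and night recovery, and mental and physical health". Table 1, presented there as the full set of outcomes, separates sleep from nighttime recovery and so has six primary rows. Most rows hold several measures and none is ranked. The health row, for example, begins "Self-reported injuries, general health, mental health (MHI-5" and also includes burnout. The first hypothesis (Hypotheses section) gathers all the domains under one overall effect.

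**Sample size.** The Sample Size Calculation section is for a "2-arm, parallel-group superiority RCT with a continuous outcome and 1:1 allocation". The alpha term "is the critical value for a 2-sided significance level (*α* = .05", and the beta term "is the critical value corresponding to 80% power". The standard deviation and the target difference come from an earlier study of office workers in which "daily recovery was defined as the normalized difference between so-called “body battery levels" in the evening and at wake-up. The regression was fitted "with recovery in body battery levels as the dependent variable". Neither quantity is given as a number. The stated total is about 330 to 370, and 350 were enrolled.

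**The nearest outcome row.** Nighttime recovery is measured daily by Garmin smartwatch and app questionnaire, described as "Objective physiological heart rate metrics; self-reported recovery (Karolinska sleep diary". Body battery is not named in Table 1. Figure 3, which covers the metrics, is not shown in the text reviewed.

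**The concern.** The error rate and the power are stated for one test of one endpoint. The claim they support, an overall effect of REHEAT, rests on six domains with no order between them and no rule for how many must succeed. Nor does the text say that the endpoint behind the sample size is one of the six. A reader of the final report could not tell which result the 5% and the 80% belong to.

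The risk is a choice of headline result after the data are seen. The trial is unblinded, and strain, sleep and nighttime recovery each place an objective measure beside a self-report without saying which one decides. Sleep and health also have both daily and pre/post time frames.

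**Working it through.** **Inputs.** Two-sided alpha 0.05, power 80%, 1:1 allocation, total 330 to 370, margin about 10% (Sample Size Calculation); 350 enrolled (Results); six primary rows (Table 1). Counting measures row by row (strain, cognition, affect, sleep, recovery, health) gives 3 + 2 + 1 + 4 + 2 + 4 = 16, or 17 if positive and negative affect are separated.

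**1. The plan's own figure.** The formula is n = 2σ²(Z_α/2 + Z_β)²/Δ² per group. With no σ or Δ given, N cannot be derived forwards, only solved backwards for d = Δ/σ:

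- N = 330 (165 per arm): d = (1.960 + 0.842) × √(2/165) = 0.308
- N = 350: d = 0.300
- N = 370: d = 0.291

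The margin fits: 330 × 1.10 = 363 and 330/0.90 = 367, close to the upper figure of 370. The calculations below treat 330 as the base N. At that d and a single 5% test, all 350 participants give 82% power; if 10% are lost (315), it is 78%.

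**2. Error rate if any one success counts, each test at 5%.** Under independence this is 1 − 0.95^k: 1 − 0.95⁶ = 0.265 and 1 − 0.95¹⁶ = 0.560. For correlated tests, simulation with equally correlated normal statistics gives:

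| Correlation | 6 tests | 16 tests |
|---|---|---|
| 0 | 27% | 56% |
| 0.3 | 24% | 48% |
| 0.5 | 21% | 38% |
| 0.7 | 16% | 26% |
| 0.9 | 11% | 15% |

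**3. Power for one endpoint if alpha is split.** Power ≈ Φ(d√(n/2) − Z), with n per arm.

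- Six domains, alpha 0.05/6 = 0.00833, Z = 2.638. At N = 330: Φ(2.802 − 2.638) = 56%. At N = 350: Φ(2.885 − 2.638) = 60%. At 315: 54%.
- Sixteen measures, alpha 0.05/16 = 0.003125: 44% at N = 330 and 47% at N = 350.

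The 56% does not depend on the value of d. Any design with exactly 80% power at 5% has 2.802 in this position. The 60% does depend on 330 being the base N.

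To regain 80% with six, n must rise by (2.638 + 0.842)²/(1.960 + 0.842)² = 1.54. That is about 255 per arm, 510 in total, or 567 after dividing by 0.90 for dropout.

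**4. Power if all six must succeed.** The error rate stays at or below 5%. Granting 80% to each domain, joint power is 0.8⁶ = 26% under independence, 48% at correlation 0.5 and 68% at 0.9.

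**5. One named primary at the full 5%.** The stated N keeps 80% power for d = 0.308. Of the rules examined here, only this one keeps both stated properties.

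**The case against.** The strongest reply is that the article states no decision rule. A reader might infer that the first hypothesis counts success on any one domain. It does not say so: it lists the domains together, with neither an any nor an all. The Statistical Analysis Plan section does not say that outcomes will be tested unadjusted, and a separate SAP may set the adjustment. This stands, so the error rates in step 2 are conditional.

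A reader might also infer that neither the 5% nor the 80% holds. The documents do not support that. The 80% for body-battery recovery tested alone at 5% is not refuted, and for the other domains power is simply not established. Nor is a chance finding very likely across six domains, at 11% to 27%.

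A further tempting reading is that the powered endpoint is not an outcome of the trial at all. Nighttime recovery shares the type of device, the daily timing and the overnight concept, and the missing Figure 3 might name body battery. What stands is that the text does not make the link.

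The reply does not remove the point. Which outcome is primary, and which endpoint and alpha justify N, are protocol-level choices that this article makes. A SAP could supply an adjustment, but any of the usual rules for six primaries gives up either the 5% or the 80%, as steps 2 to 4 show.

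**Conclusion.** The point holds in this form: one endpoint is powered at an undivided 5%, six unordered domains are called primary, and the powered endpoint is tied to no row.

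Its size depends on the rule eventually adopted:

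- **Any one counts, unadjusted:** false-positive chance of about 11% to 27% for six domains and 15% to 56% for 16 measures, over correlations from 0.9 down to 0.
- **Bonferroni over six:** about 56% power at N = 330 and 60% at N = 350.
- **All six required:** joint power of about 26% to 68%.

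The assumptions are a base N of 330 with back-solved d of about 0.31, equal correlation between tests, the normal two-sample formula rather than the planned mixed models, and, for the joint figure, 80% power in every domain. The missing link and the missing order need none of these assumptions.

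**What to change.** Make one of two changes before any outcome data are accessed. The article reports that none had been at submission, but preliminary analyses are planned for late fall 2025.

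1. **Preferred.** State in the Nighttime recovery row of Table 1 that the measure is body-battery recovery as defined for the sample size, if it is collected. Name it the single primary outcome at two-sided 5%. Make the other five domains key secondary outcomes, with one named measure each and Holm adjustment.
2. **Alternative.** Keep six primaries with one named measure per domain under Holm at 5%. Restate the power as about 56% to 60% at the first Holm step for an endpoint with d of about 0.31.

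In both cases, report σ and Δ so that the calculation can be checked. If body battery is not collected, the first option is not available, and the article should say that the sample size rests on a proxy.

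The cost is wording in the protocol, SAP and registry entry, with no new participants. Under the first option five domains lose co-primary status; under the second the stated power falls. Either change must be dated and recorded as made during data collection but before access to outcome data.

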### Sample Size Calculation

We estimate the minimum sample size for a 2-arm, parallel-group superiority RCT with a continuous outcome and 1:1 allocation using the standard formula:

$$n=\frac{2\sigma^{2}{\left(Z_{\alpha /2}+Z_{\beta }\right)}^{2}}{\Delta^{2}}$$

where *n* is the required sample size per group, *σ* is the standard deviation of the outcome, ∆ is the expected difference (minimum clinically important difference) between groups, *Z_α/_*_2_ is the critical value for a 2-sided significance level (*α* = .05), and *Z_
_β_
_* is the critical value corresponding to 80% power.

To inform the parameters *σ* and ∆, we use empirical data from a previous observational study conducted by the REHEAT research team on a sample of 294 office workers in Canton Ticino (Southern Switzerland), monitored for 30 working days between February and April 2024.^
45
^ In that study, daily recovery was defined as the normalized difference between so-called “body battery levels” (a measure assessed by means of smartwatches) in the evening and at wake-up. A fixed-effects panel regression model is estimated, with recovery in body battery levels as the dependent variable and average daily temperature (from the Lugano MeteoSwiss station) as the main predictor, controlling for perceived health, weekday, and week number.

Due to the absence of days with average temperatures above 18^◦^C in that dataset, we extrapolate the expected effect of hot days by assuming a linear relationship between temperature and recovery. We use predicted average recovery values for moderate days (14°C-18°C, typical of June in Canton Ticino) as the baseline and compare them to predicted values at 25°C—the MeteoSwiss threshold for heat episodes.^
56
^ The resulting difference in recovery is used as the expected intervention effect (∆), under the assumption that the REHEAT strategy could fully mitigate the adverse impact of heat.

Although optimistic, this assumption is conservative in terms of sample size estimation: the effect size is derived from a lower-risk population (office workers) and under the assumption of linearity, whereas prior literature suggests that the impact of heat on health is often nonlinear and intensifies at higher temperatures.

While the sample size is calculated based on a simple 2-sample comparison, the planned analyses will employ mixed-effects models, which account for repeated measures and hierarchical data structures and are therefore more complex than a simple *t*-test. To ensure adequate power and to compensate for potential design inefficiencies associated with these models, as well as expected dropout, we add a safety margin by increasing the total number of participants by about 10%.

Based on that analysis, we determine that a total sample ranging from approximately 330 to 370 participants would provide sufficient power to detect the estimated effect, with the upper bound reflecting an additional safety margin to account for potential dropout and model complexity.

### Statistical Analysis Plan

The evaluation of the REHEAT heat adaptation strategy consider the following 4 areas: implementation and compliance, impact, heterogeneity, and satisfaction.

Implementation and compliance: descriptive statistics and inferential comparisons assess baseline equivalence between treatment and control group and participant compliance across relevant sociodemographic characteristics, work experience, health condition, and selected outcomes. App usage data is analyzed using frequency distributions and stratified analyses by age, sex, and location to ascertain user engagement with the app.Impact Analysis: The impact of the REHEAT strategy is first evaluated using an Intention-To-Treat (ITT) approach, which yields the most reliable estimates for real-world interventions by preserving the benefits of randomization. In parallel, Local Average Treatment Effects (LATE) are estimated to assess the intervention’s effects at varying levels of participants’ potential heat exposure and compliance. ITT analyses are conducted at the individual level. The effects of REHEAT on the primary outcomes—measured at on-boarding and off-boarding—as well as on those monitored throughout the summer, are estimated using random-intercept mixed-effects models. By accounting for within-subject correlations over time, this approach supports a robust analysis of longitudinal data. LATE estimates on primary outcomes are derived using instrumental variable generalized linear mixed models (IV-GLMM), with MeteoSwiss weather data and REHEAT app usage serving as instruments. Specifically, passively recorded data on the frequency of use of the app’s features over time are used as a proxy for participants’ compliance with the intervention. These models control for randomization strata and blocks, as well as a set of time-invariant and time-varying co-variates deemed theoretically or empirically relevant. Because heat effects vary across time, cumulative exposure, and acclimatization,^57,58^ temporal factors are explicitly controlled in the analyses. Exposure to heat is modeled using distributed lag models to capture both immediate and delayed effects of temperature and humidex across pre-specified lag periods. Mixed-effects models include calendar-week splines, random slopes for time, and adjustments for survey date and recent mean temperature to account for differences in measurement timing and seasonal acclimatization.^
59
^ Potential time-invariant characteristics of the respondents (eg, years of experience in home care, chronic conditions), and time-varying confounding due to intermediate variables (eg, workload changes, night shifts) are also addressed in sensitivity analyses.

Effect Heterogeneity: interaction terms are included in multilevel models to explore differences in outcomes by sex, age, geographical region, and time-related factors. Separate models assess moderation effects by these variables in both ITT and LATE frameworks. Random intercept multilevel regression techniques are used to model hierarchical longitudinal data that violate the independence assumption (ie, repeatedly measured continuous outcomes). The heterogeneity of heat episode effects are estimated by multiple-interaction models in which interaction terms between the heat episode, the participant’s area of work, age, and sex are estimated. To capture temporal heterogeneity, additional interaction terms assess whether the REHEAT strategy differentially mitigates heat effects over the course of the summer. Treatment-by-time interactions, such as calendar week, cumulative heat exposure, or time since onboarding, are used to examine whether intervention effects vary due to seasonal acclimatization or repeated exposure.^
59
^ Flexible calendar-week splines and random slopes for time allow for individual adaptation trajectories and evolving heat vulnerability. These analyses determine whether the REHEAT strategy effectively addresses the diverse and changing needs of home care workers operating in different areas of Switzerland, who are exposed to different climatic, organizational and contextual conditions, while also estimating average conditional treatment effects across demographic and temporal dimensions.

Satisfaction: Participants’ satisfaction is evaluated using a mixed-methods approach, combining quantitative survey data with qualitative insights. Qualitative data are collected through interviews with a small randomly selected sample of home care workers, drawn from the pool of study participants. The sampling ensures representation across key variables relevant to the study, such as geographical area, sex, and age. Selected individuals are contacted at the end of the study and invited to voluntarily share their experiences in either an online or face-to-face interview. Collected data are analyzed via thematic analysis, employing inductive coding strategies and inter-rater reliability checks. Quantitative data are obtained through a user experience questionnaire administered to all participants during the off-boarding phase, at the end of the RCT. The questionnaire aims to assess participants’ overall satisfaction and experience with the REHEAT study and, for those in the treatment group only, the perceived usefulness of the suggested REHEAT strategy.Contamination: Additionally, specific items are included in the offboarding questionnaire to gather information on any potential contamination that may occurr during the treatment period. Assessing contamination is essential in studies such as REHEAT that are conducted within organizational settings, where interactions among participants may lead to unintended exposure of control group members to elements of the intervention. Systematically examining potential contamination allows for a more accurate interpretation of the findings and strengthens the credibility of causal inferences.Handling of missing data: Missing data are addressed through multiple imputation using chained equations (MICE).^
60
^ For time-series of physiological data, additional methods such as temporal smoothing, regression-based imputation, and complete-case sensitivity analyses are used.

Quantitative analyses are carried out using STATA 19,^
61
^ R,^62,63^ and Python.^
64
^ Qualitative data are analyzed using dedicated software for qualitative research, specifically MAXQDA or NVivo.

